## **7. Study period**

Approximately 3.6 years (Recruitment – 2 years; Intervention and assessment – 1.6 years)

### ***A. Recruitment***

Approximately 2 years (June 2022 ~ May 2024)

### ***B. Intervention***

One year after the enrollment

### ***C. Follow-up period***

About 1.6 years (18 months) from the enrollment (including the intervention period)

## **9. Study participants' enrollment and initial assessment**

### **A. Patient's Registration for the Clinical Trial and Initial Assessment**

#### ***1) Patient Recruitment***

- Post the recruitment information in the outpatient and inpatient wards and public bulletin boards of the participating institutions. Explain the study to the patients and their guardians who meet the inclusion criteria in the outpatient or inpatient ward of co-investigators and

register consenting patients.

- Explain the study to inpatients, outpatients, and their guardians who meet all inclusion criteria and none of the exclusion criteria at each participating institution. Obtain written informed consent from the patients who agree to participate in the study. Similarly, obtain separate written informed consent from their guardians.
- The patient's unique identification information (i.e., resident registration number) will be collected on the consent form for participation in the clinical trial to collect secondary data. Patients will check a separate box for providing their consent to allow the access and use of their data (e.g., data from the National Health Insurance Service and Health Insurance Review and Assessment Service, Statistic Korea's data on death, and data from the Korea National Institute for Bioethics Policy).

## ***2) Initial assessment and education for patients and their family caregivers***

An initial assessment will be conducted at the time of patient enrollment. Nurses will assess patients regarding their demographic information, past medical history, current medical condition, QoL, symptoms, emotional status, care burden, care ability, pharmaceutical history, symptom control status, and medical device usage. Patients will receive educational materials and have a one-on-one education session on symptom control (15 min), medication counseling, medical device management, and critical symptoms that must be reported to nurses.

- The research nurse will provide home care education materials (to be developed) at the initial assessment that will include the following contents.

| Category           | Content                                                                         |
|--------------------|---------------------------------------------------------------------------------|
| Pain Management    | Types of analgesics and the methods of administration                           |
| Symptom Management | Types of symptoms that patients may experience and ways to control them at home |
| Home Care          | Ways to manage the home care environment                                        |

## **B. Intervention**

### ***1) Multidisciplinary team***

The institutions in the intervention group will establish home-based medical teams comprising doctors, nurses, and social workers. The doctors will be home-based care specialists and/or hematologist-oncologists. The nurses will be dedicated home-based medical intervention nurses who would be newly recruited and receive home-based medical intervention training for more than 3 months. Professional medical staff will provide the educational program, consisting of lectures to understand palliative care and symptoms of patients with advanced cancer and HBMC program simulation training.

### ***2) Additional assessment and education***

An initial assessment will be conducted at the time of patient enrollment. Nurses will assess patients regarding their demographic information, past medical history, current medical condition, QoL, symptoms, emotional status, care burden, care ability, pharmaceutical history, symptom control status, and medical device usage. Patients will receive the educational materials and have a one-on-one education session on symptom control (15 min), medication counseling, medical device management, and critical symptoms that must be reported to nurses.

| Category                                                 | Content                                                                            |
|----------------------------------------------------------|------------------------------------------------------------------------------------|
| Symptom Management                                       | Types of symptoms that patients may experience and ways to control them at home    |
| Medication Administration                                | Types of medication prescribed to patients and the methods of administration       |
| Medical Device Management Methods                        | Methods to manage medical devices in case a patient possesses a device             |
| Items that must be Reported to a Healthcare Professional | Types and intensity of symptoms that must be reported to a healthcare professional |

### ***3) Home visits by nurses***

Nurses in the team will visit the enrolled patient's home within 2 weeks of the initial

assessment. They will make an appointment for a home visit when both the patient and their family caregiver are available. Next, they will assess the home environment for the patient's care, medication, and medical device management. Patients will be educated regarding the condition of their home environment, fall prevention, symptom management, medication counseling, medical device management, and critical symptoms that need to be reported to nurses.

- The medical staff on the HBMC team will evaluate the following items at patients' homes.

| Category                         | Content                                                                                                                                                   |
|----------------------------------|-----------------------------------------------------------------------------------------------------------------------------------------------------------|
| Home Care Environment            | Risk factors in patients' homes (e.g., rooms, living rooms, and bathrooms); potential risk of falls; proper management of medications and medical devices |
| Medication Administration        | Types of medication a patient has or is currently taking along with the medications prescribed by the institution and the methods of administration       |
| Medical Device Management Status | Whether patients are using medical devices appropriately at home in case they possess a device                                                            |
| Symptoms and Dietary Intake      | Assess the symptoms reported by the patient and their dietary intake                                                                                      |
| Performance Status               | ECOG performance status, CFS score                                                                                                                        |
| Vital Signs                      | Assessment of blood pressure, pulse rate, respiratory rate, body temperature, and oxygen saturation after the registration at the first visit             |

- The medical staff on the HBMC team will evaluate the following items at patients' homes. If adjustments to the home care environment besides the content covered in the initial training are necessary, then education on the relevant content will be provided.

| Category                                                 | Content                                                                                                                                                                                                       |
|----------------------------------------------------------|---------------------------------------------------------------------------------------------------------------------------------------------------------------------------------------------------------------|
| Adjustment of Home Care Environment                      | Discuss methods of adjusting the home care environment if a risk factor is identified in a patient's home
- E.g., installing non-slip mattresses and power generators for emergency oxygen systems at home |
| Symptom Management                                       | Types of symptoms that patients may experience and ways to control them at home                                                                                                                               |
| Medication Administration                                | Types of medication prescribed to patients and the methods of administration                                                                                                                                  |
| Medical Device Management Methods                        | Methods to manage medical devices in case a patient possesses a device                                                                                                                                        |
| Items that must be Reported to a Healthcare Professional | Types and intensity of symptoms that must be reported to a healthcare professional                                                                                                                            |

#### ***4) Monthly multidisciplinary team meeting***

A multidisciplinary team meeting of specialized home-based medical teams will be organized once a month. Team meeting agendas are as follows: sharing information on patients enrolled in the study, establishing a care plan for the participants, and regularly reassessing the patients to adjust the care plan. The care plan includes the objectives of home care based on the patient's assessment, symptom management, additional medical needs at home, and reported critical symptoms.

- The care plans established and periodically modified in the multidisciplinary team meetings will include the following.

| Category                                                 | Content                                                                                                                                                                                                                                                                                                                                                                                                                                                                                                                                                                                                                                                                                                                                                                                                                                                                                                                                                                      |
|----------------------------------------------------------|------------------------------------------------------------------------------------------------------------------------------------------------------------------------------------------------------------------------------------------------------------------------------------------------------------------------------------------------------------------------------------------------------------------------------------------------------------------------------------------------------------------------------------------------------------------------------------------------------------------------------------------------------------------------------------------------------------------------------------------------------------------------------------------------------------------------------------------------------------------------------------------------------------------------------------------------------------------------------|
| Care Goal Setting                                        | Establish care goals at the patient's home based on the assessment results of the patient and guardian (i.e., caregiver). 

- Determine the duration for which the patient wishes to stay at home and the circumstances under which the patient wants to be hospitalized

- Check the patient's and guardian's intention for life-sustaining treatments

                                                                                                                                                                                                                                                                                                                                                                                                                                                                                                                                                                 |
| Symptom Management                                       | Present types of symptoms that the patient may experience and ways to handle them at home. 

1. For symptoms for which the patient has medication, the HBMC team nurse will educate the patient on how to take the medication and observe whether the symptoms improve.

2. For newly occurring symptoms or symptoms that are not controlled by taking the existing medications, the HBMC team nurse will contact the HBMC team physician to discuss whether or not additional medications should be prescribed.

3. When a consultation with a physician is necessary, such as if an additional medication prescription is required, the HBMC team nurse will consult with the HBMC team physician to schedule an outpatient visit and inform the patient and guardian.

4. If hospitalization or ER visit is required, the HBMC team nurse will contact the patient and their caregiver to inform them.

 |
| Home Care Management Plan                                | Determine whether additional management or visits are required besides biweekly routine management. 

- A HBMC team nurse will make additional visits to provide training if additional training is required regarding items included in the education, such as symptom management and medication administration, or if the patient or guardian wishes additional visits.

- Patients at high risk for worsening symptoms will be contacted within a week after establishing a care plan to identify changes in their condition.

                                                                                                                                                                                                                                                                                                                                                                                        |
| Items that must be Reported to a Healthcare Professional | A HBMC team nurse will share any symptoms or possible incidents that require reporting to the HBMC team physician throughout the routine management period. Commonly included items are: 

- Pain of numerous rating scale (NRS) score of 7 or higher persists while on

                                                                                                                                                                                                                                                                                                                                                                                                                                                                                                                                                                                                                                                        |

|  |                                                                                                                                                                                                                                                                                       |
|--|---------------------------------------------------------------------------------------------------------------------------------------------------------------------------------------------------------------------------------------------------------------------------------------|
|  | medication
- Uncontrolled symptoms persist while on medication
- Occurrence of issues in the use of a medical device that are difficult for a nurse to evaluate or train
- Changes in the care provider's care environment (such as difficulty in providing continuous care) |
|--|---------------------------------------------------------------------------------------------------------------------------------------------------------------------------------------------------------------------------------------------------------------------------------------|

### ***5) Home Care Management***

The nurses will contact the patients biweekly via telephone and assess the status of their symptoms. The assessment will include their symptom status, medication adherence, medical device management, home environment for caring, and any requirements of patients and family caregivers. The team doctor will review the assessment, and if necessary, decide to provide medication/medical device adjustment, education, and guidance on visiting the ER. If the patient assessment is insufficient via telephone or in-person patient education is required, the nurses will visit the patient's home.

- A nurse on the HBMC team will evaluate the following items at patients' homes during the routine home care management check.

| Category                  | Content                                                                                           |
|---------------------------|---------------------------------------------------------------------------------------------------|
| Performance Status        | ECOG performance status, CFS score                                                                |
| Symptom Management        | Presence or absence of symptoms, exacerbation, or alleviation compared to previous assessments    |
| Medication Administration | Check whether medications are being taken as prescribed
If not, then identify the reason(s)    |
| Medical Device Status     | Ensure that medical devices are operating without abnormalities if the patient possesses a device |
| Miscellaneous             | Check for anything the patient and guardian wish to consult with the medical staff                |

A daytime telephone number to contact the home care medical team nurse between 9 AM to 5 PM on weekdays will be provided to the study participants. If they have any questions or concerns, they can leave a message for the nurse via an access line. The nurse will call the patient and their caregiver to consult about their symptoms, events, or any concerns about the patient's status.

A multidisciplinary team meeting of specialized home-based medical teams will be organized once a month. Team meeting agendas are as follows: sharing information on patients enrolled in

the study, establishing a care plan for participants, and regularly reassessing the patients to adjust their care plan. The care plan will include the objectives of home care based on the patient's assessment, symptom management, additional medical needs at home, and reported critical symptoms.

## 2. Control

Patients enrolled in the control cluster (institution) will receive educational materials. These patients will continue to receive the usual oncology care.

- If a patient in the control group moves to an intervention group institution for the follow-up, the patient will be excluded from the clinical trial.

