| Statistical Analysis         | 
The HBMC intervention group, control group, and each participating institution will be set as analysis groups for the statistical analysis of the outcome variables.
 
The analysis groups of the participants are based on the group assignment according to the initial intention-to-treat (ITT) that relies solely on the intervention of the original assignment to estimate the effectiveness in the intervention group conservatively. In the case of withdrawal of consent or dropout during follow-up, data collected till the time of withdrawal or dropout will be used. A comparative analysis of the dropout rate between the two groups will be performed and reported.
 
 
- Descriptive analysis of underlying characteristics
 
 
Continuous variables: mean (standard deviation) and median (IQR)
 
Dichotomous variables: frequency (%)
 
 
- Analysis of between-group differences
 
 
An analysis will be performed using a regression model while considering that participants, the observation units, were clustered into six participating institutions to evaluate the effects of the HBMC intervention and correcting for the differences in the baseline characteristics between the groups.
 
Dichotomous variable (primary endpoint): A generalized estimation equation (GEE) will be used to analyze the clusters of patients in participating institutions, and the effects of the HBMC intervention will be evaluated using a logistic regression model based on the logit link function.
 
Continuous variables: The effects of the HBMC intervention will be evaluated using a mixed model to consider the patient clusters in the participating institutions.
 
Count data: A GEE will be used to consider the patient clusters in the participating institutions, and the effects of the HBMC intervention will be evaluated using a regression model that appropriately uses Poisson and negative binomial as random components according to the distribution of variables using the logit link function as the link function.
 |

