## **13. Suspension and Dropout Procedures**

### **A. Clinical Trial Suspension Criteria**

- The clinical trial will be suspended in the following cases.

1. When a patient or their caregiver wishes to discontinue the HBMC intervention
2. When a participant passes away
3. When a participant is hospitalized at a medical institution for an additional four weeks
4. When a patient's treatment at the hemato-oncology department of the respective hospital has been terminated or follow-up has been discontinued
5. When a participant uses an inpatient or home-based hospice care services
6. When the suspension of participation in the clinical trial is deemed best for the participant at the investigator's discretion
7. When a participant does not cooperate with the physician in charge of the clinical trial or does not follow the physician's instructions
8. When the regulatory authority, ethics committee, or Institutional Review Board (IRB) suspends the clinical trial

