## **C. Follow-up of Suspended Participants**

- Investigation of the medical records and secondary data linkage will be performed on the suspended participants from the time of suspension to the end of the remaining scheduled follow-up period (18 months after the registration) until no longer possible due to the participant's death, failure to follow-up, or withdrawal of consent. Any case of a patient receiving additional HBMC services (e.g., other HBMC pilot projects) other than the one provided in this clinical trial after the completion of the study will be recorded in the care

reports.

- For participants suspended due to reasons other than death, the follow-up survey will only be conducted with those who consent to participate via a telephone call made by a research nurse.

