### ***4) Statistical analysis***

Definition of home-based medical service intervention group and study dropouts: Patients who provided informed consent to the selected home-based medical service intervention institutions and control group institutions are defined as the intervention group and control group, respectively. Based on the principle of group classification by intention-to-treat (ITT) that only considers the initial classification of intervention, omission of home-based medical service is still defined as the intervention group, which causes a bias that reduces the effects in the treatment group. Despite the study's design to conservatively estimate the effects in the treatment group, if significant differences are observed in the results among patients who withdraw consent or dropout during follow-up, data up to the point of withdrawal of consent or dropout will be used. Dropout rates will be analyzed and reported for each group.

The mean proportion of unplanned hospitalization will be compared between the intervention and control groups for the primary outcome. The mean of continuous variables and a fraction of dichotomous variables for each item in domains one to five will be compared between the two groups for the secondary outcome. A generalized estimation equation will be used to evaluate intra-group correlations to compensate for clusters of patients in the participating institutions. Survival after enrollment will be compared using the Kaplan-Meier curve and Cox proportional hazard model.

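### Control patients who move to an intervention hospital are excluded from the trial, with no matching rule for the intervention arm, in conflict with the protocol's intention-to-treat grouping and its follow-up rule for patients who leave the enrolling hospital

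*Protocol*

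**What the plan says.** The Control subsection, placed after section 9.B (Intervention), states: "If a patient in the control group moves to an intervention group institution for the follow-up, the patient will be excluded from the clinical trial". The trigger is the move itself, not receipt of home-based medical care (HBMC). The rule has no time limit, although follow-up runs to about 18 months (section 7.C) and the primary endpoint closes at 6 months (section 12.A).

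Two places define the analysis groups. In the overview, under Statistical Analysis, they follow the "initial intention-to-treat (ITT) that relies solely on the intervention of the original assignment". Section 14.B.4 has the same rule, "Based on the principle of group classification by intention-to-treat (ITT) that only considers the initial classification of intervention", and adds that "omission of home-based medical service is still defined as the intervention group".

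The protocol also has a general provision for leaving the enrolling hospital. The fourth suspension criterion in section 13.A reads "When a patient's treatment at the hemato-oncology department of the respective hospital has been terminated or follow-up has been discontinued" and is not limited to one arm. Section 13.C then continues record review and linkage "from the time of suspension to the end of the remaining scheduled follow-up period", that is, to 18 months after registration unless death, loss to follow-up or withdrawal of consent intervenes. The overview gives a similar rule for this suspension reason.

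No sentence addresses an intervention patient who moves to a control hospital.

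**The concern.** A control patient who moves to an intervention hospital falls under two incompatible instructions. The analysis sections keep the patient in the control group, and section 13.C keeps the outcome under observation. The Control subsection takes the patient out of the trial.

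Moving happens after enrolment and may be related to disease course, dissatisfaction with care or an acute admission, so it may be related to the primary outcome. Selecting on it in one arm only adds a bias that adjustment for baseline characteristics cannot be relied on to remove. The trial is non-randomised with three hospitals per arm, so it already depends on that adjustment and has little room for a further source of imbalance.

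The rule also reaches further than contamination control needs. Read literally, it excludes a control patient who moves at month 9 with a complete 6-month outcome, and one who moves but never receives HBMC.

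**Working it through.** **Step 1. The same event in each arm**

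| Event | Control arm | Intervention arm |
|---|---|---|
| Treatment or follow-up at the enrolling hospital ends | Suspended; records and linkage continue (13.A, 13.C) | Same |
| Patient moves to a hospital of the other arm | Excluded from the trial (Control subsection) | No rule; by inference from 13.A, 13.C and 14.B.4, stays in group and under follow-up |
| Analysis group | Initial classification (overview, 14.B.4) | Same |

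Only the middle row differs by arm. Its control cell contradicts the rows above and below it.

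**Step 2. What exclusion could mean**

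- *Removal from the analysis.* The control arm then consists only of patients who did not move.
- *Handling as a dropout.* The overview would keep data collected up to that point. An event before the move counts; an event after it is not observed. If such a patient is coded as having no event, the control rate is understated. The size depends on how many movers have their first event after the move and on how an incomplete window is coded. The protocol gives neither, so I put no figure on this reading.

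Under both readings the distortion falls on the control arm alone.

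**Step 3. Size under full removal**

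The protocol states no figure for movers, so there is none to reproduce. Let p be the true control event rate, f the fraction of controls who move and q the event rate in movers. With no true effect:

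- remaining control rate = (p − f·q)/(1 − f)
- false difference, intervention minus control = p − remaining rate = f·(q − p)/(1 − f)

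Inputs: 198 controls (section 6). The 20% rate is close to the 40/198 in the section 6 table. The 50% rate, f = 5-10% (about 10 to 20 patients) and q = 0.5 to 2 times p are assumptions.

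| p | f | q | Remaining control rate | False difference (points) |
|---|---|---|---|---|
| 20% | 5% | 10% | 0.195/0.95 = 20.5% | −0.5 |
| 20% | 5% | 40% | 0.180/0.95 = 18.9% | +1.1 |
| 20% | 10% | 10% | 0.190/0.90 = 21.1% | −1.1 |
| 20% | 10% | 40% | 0.160/0.90 = 17.8% | +2.2 |
| 50% | 5% | 25% | 0.4875/0.95 = 51.3% | −1.3 |
| 50% | 5% | 100% | 0.450/0.95 = 47.4% | +2.6 |
| 50% | 10% | 25% | 0.475/0.90 = 52.8% | −2.8 |
| 50% | 10% | 100% | 0.400/0.90 = 44.4% | +5.6 |

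Higher-risk movers make the intervention look worse; lower-risk movers make it look better; movers at the control risk give zero.

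Two cases outside the grid:

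- *Few movers:* 2 of 198 at p = 50% and q = 75% gives (99 − 1.5)/196 = 49.7%, a shift of 0.3 points.
- *Extreme:* at 40/198, with 10% movers who all have an event, (40 − 19.8)/178.2 = 11.3%, a shift of 8.9 points. This needs movers at about five times the control risk (1/0.202).

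For scale, the assumed effect is 20%, without saying whether absolute or relative. The section 6 table's 40/198 against 20/198 is 10.1 points.

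**Step 4. Power**

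Assume 50% against 30%, two-sided 0.05, ICC 0.015 and 66 per cluster, so the design effect is 1 + 65 × 0.015 = 1.975. Power is then 0.840. Losing 10% of controls lowers it to 0.829. The issue is bias, not power.

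**The case against.** The strongest reply is that this is a sensible guard against contamination, and that the text supports less than it might seem. Four parts of that reply stand.

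- A reader might infer that control movers' data are deleted. The protocol does not say so. The overview's dropout rule could preserve data up to the move, and the Step 3 figures apply only to full removal.
- A reader might infer that the protocol expressly keeps intervention movers in. It does not. This follows from the absence of a mirror rule together with sections 13.A, 13.C and 14.B.4. Nothing in the document points the other way.
- The mover fraction and the movers' risk are assumptions. Only a move for follow-up to one of three named hospitals triggers the rule, so the number affected could be very small.
- Section 14.B.4 presents intention-to-treat as a principle of group classification, and with no randomisation there is no randomised comparison to protect.

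The last part does not remove the conflict. A group defined only by initial classification cannot also lose members because of where they later seek care, and section 13.C expressly continues observation of patients who leave the enrolling hospital. Contamination by a few movers is the kind of dilution that section 14.B.4 already accepts when HBMC is not delivered in the intervention arm.

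A reader might also infer from the endpoint definition that an admission at another trial hospital counts under neither part of it. The wording can equally be read as covering any participating institution, and any gap would affect both arms. That is a separate, minor clarification and not part of this point.

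**Conclusion.** The point holds. The Control subsection applies a post-enrolment exclusion to one arm, against the intention-to-treat grouping in the overview and section 14.B.4 and against continued follow-up under section 13.C. Whichever meaning of exclusion applies, the 6-month primary outcome of control movers is selected or truncated, with no corresponding rule in the intervention arm.

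The document does not support a stronger statement that the result is biased by a known amount or in a known direction. Under the stated assumptions and full removal, the false difference is roughly 0.5 to 2 points at a 20% control rate and up to about 6 points at 50%, with either sign. It is negligible if movers are rare and exceeds this range only if movers' risk is far above that of other controls. The contradiction itself rests on none of these assumptions.

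**What to change.** Reconcile the Control subsection with the overview's Statistical Analysis entry and sections 13.C and 14.B.4, by replacing the exclusion sentence with one to this effect:

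> For the primary analysis, a patient in either group who moves to another participating institution remains in the group of the enrolling institution. Outcome collection through records and linkage continues, subject to consent, to the end of follow-up. The date of the move and any HBMC received are recorded.

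Any exclusion of movers belongs in a sensitivity analysis that applies the same rule to both arms. The suspension criteria need not change for this. If any control patient has already been excluded under the current sentence, report the number by hospital and recover the 6-month outcome where consent allows.

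The cost is one amended sentence with IRB approval and two added data items. Two practical points go with it. Section 11.B surveys records at the respective institution, so access to a mover's records at the receiving hospital must be arranged. Section 11.C describes linkage for the intervention group, whereas the overview describes it for consenting patients generally; these need aligning so that linkage for control movers has a clear basis.

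The statistical downside is slight dilution of the contrast if some control movers receive HBMC.
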